**Figure 1 figure1:**
[figure not shown]
Recruitment and assessment timeline for the ¡Alégrate! web-based intervention.

### Content of the Intervention

Our Spanish-language web-based *¡Alégrate!* positive psychological intervention was adapted from previously published and empirically validated curricula of the Moskowitz MARIGOLD trial [37-41]. Our 5-week *¡Alégrate!* intervention delivers curricular content via didactic instruction (eg, text, videos), journaling, and assigned at-home practice—all accessed via our website using investigator-purchased tablet computers. The website was designed and managed by [name], a coinvestigator of the *¡Alégrate!* intervention. This 5-session, multicomponent web-based intervention instructs on 8 emotion regulation skills that have proven efficacious for increasing positive emotion and decreasing symptoms of depression and psychological distress in patients with varying chronic illness diagnoses, that is, those with metastatic breast cancer, HIV, and type 2 diabetes [38,40,41]. A detailed description of the curricula is published elsewhere [42]. Briefly, 8 empirically validated behavioral and cognitive skills are taught via our web-based interface, and include the following: (1) identification and use of personal strengths; (2) noticing of positive events in daily life; (3) prolonged appreciation and relishing of positive events; (4) positive reappraisal of stressful events or situations; (5) gratitude; (6) regular practice of mindfulness and meditation; (7) setting and working toward pragmatic and achievable goals; and (8) planning and performing acts of kindness. We previously tested the in-person delivery of MARIGOLD in the Spanish language [19].

During each weekly session, participants will learn skills and then complete the assigned at-home exercises to actively integrate the acquired techniques into daily life. As such, participants are instructed to log-in to the *¡Alégrate!* website for 30-min sessions at least three times per week. New skills are sequentially taught every week (see Table 1 for sequencing and content); to ensure successive instruction, new content becomes available only after a 7-day period, and once participants have completed the previous week’s content and at-home practice. Table 1 summarizes the content of the *¡Alégrate!* Spanish-language curricula, and Figure 2 presents screenshots of our web-based curricular interface [43]. Each participant logs in to the *¡Alégrate!* website using a unique username and password assigned by research staff—the tablet interface is customized with shortcuts for ease of navigation. Participants are also instructed to password protect their tablet to mitigate any data breaches from external parties.

In addition to accessing our web-based positive psychological intervention, participants will also receive weekly phone calls and text messages to reinforce lessons learned and as a strategy to maximize retention and continued visitation to our study site. Weekly phone calls will be brief, 10 to 15 min in duration, in which study staff review highlights of skills taught that week—along with technical support on any issues in handling the tablet computer or in navigating the *¡Alégrate!* site. Finally, participants with cell phone capability will receive a weekly text message from research staff highlighting the skills taught that week with the reminder to put them into daily practice—these sometimes take the form of a meme containing both images and text. For example, during Week 3 that focuses on mindfulness, they receive the following message:

Savoring requires that you slow down and pay attention to the positive events, large and small, that are happening in your day-to-day life. It can help you be more open, think more clearly, and appreciate things you have missed. It is important to be careful not to engage in thoughts that distract you from fully experiencing the present moment [La atención plena es una forma de prestar atención a los eventos positivos, grandes o pequeños, en su vida diaria. Lo puede ayudar a ser más abierto de mente, pensar más claramente y apreciar las cosas que quizás no noto. Es importante de no dedicarse en pensamientos que lo distraigan de experimentar plenamente el momento presente] 

**Table 1 table1:** Positive psychology skills imparted in the 5-week internet-based intervention.

Weekly session	Skills	Goals of the session
Week 1	Positive events and capitalizing (Skills 1 and 2)	Individuals are equipped to note positive life events in their day-to-day encounters. Capitalizing is an expressive response to positive events and includes telling others about it, marking the occurrence in some way, or even thinking about the even again later on
Week 1	Gratitude (Skill 3)	Gratitude is defined as a feeling of thankfulness and appreciation expressed toward others, which may include other people, nature, or God
Week 2	Mindfulness (Skill 4)	Mindfulness is defined as the ability to intentionally pay attention to and maintain nonjudgmental awareness of one’s thoughts, feelings, and physical sensations in the present moment
Week 3	Positive reappraisal (Skill 5)	Positive reappraisal is a form of coping in which the significance of the event is reinterpreted in a more positive way
Week 4	Focusing on personal strengths (Skill 6)	Identifying and focusing on one’s strengths as a form of self-affirmation to evaluate the resources possessed to cope with a stressful event
Week 4	Attainable goals (Skill 7)	Setting of realistic goals and imparting techniques to increase their progression and attainment
Week 5	Altruistic behaviors/acts of kindness (Skill 8)	Engagement in volunteerism and other altruistic behaviors

**Figure 2 figure2:**
[figure not shown]
Screenshots of our Spanish-language internet-based positive psychological intervention accessed via a web browser.

### Content of Control Sessions

Participants randomly assigned to the active control condition will be asked to visit the study site where they report their emotions (eg, grateful, happy, guilty, relieved, ashamed, etc), 3 times weekly, using the Differential Emotions Scale (DES), but they will not be granted access to curricular content of our *¡Alégrate!* positive psychological intervention. It takes 5 to 10 min to complete the DES online. Emotion reporting for the control condition occurs for the duration of the active intervention period, that is, 5 weeks in total. Research has previously established effectual use of emotion reporting as a control condition, with documented benefits similar to that of a placebo effect, and with high rates of retention (approximately 80%). Concerted efforts are undertaken to promote retention among participants in the control arm, including postcard notices and phone calls to remind participants to engage in web-based emotion reporting and to appear, in person, for scheduled clinical assessments. Finally, participants in the control condition will be granted access to the web-based *¡Alégrate!* curricular content upon completion of their final follow-up assessment at 12 weeks postbaseline.

Participants in both the treatment and control arms will receive detailed handouts on how to operate the *Samsung Galaxy Tab A* tablet computer, along with instructions on connecting to Wi-Fi and accessing the *¡Alégrate!* website. Handouts display textual instructions along with detailed step-by-step visual screenshots, along with a listing of Wi-Fi locations in the local neighborhood, for example, coffee shops and public libraries or bookstores. In addition, staff will hold, in person, 15- to 20-min tutorials at baseline to familiarize enrollees on tablet use, with the assurance of continual availability via phone or in person to assist with any issues and to troubleshoot difficulties encountered with the technology.

### Payment to the Participants

As compensation for their time invested and efforts in completing all trial-related tasks, participants in both trial arms (ie, treatment and active control) will be allowed to keep the investigator-purchased tablet computer at the end of the study period, which has a retail value of US $300. Participants who do not complete the full study, that is, those who drop out early, will be asked to return the tablet computer and will instead be given US $40 in cash for each assessment interview completed before dropping out. In addition, participants will receive reimbursement for travel-related costs (eg, parking, Uber, etc) and will be given light snacks while attending assessment interviews at the clinic site.

### Training and Intervention Fidelity

The principal investigator and all research staff are bilingual (English and Spanish) and bicultural (Mexican-American), and each underwent extensive training (minimum 30 hours) before recruitment and data collection. Research staff are trained to accurately implement the recruitment protocol, to properly deploy assessment interviews, and to support detailed tracking of participants throughout the 12-week study period. Over several weeks’ time, research staff were trained in the following key component areas: (1) knowledge in the protection and privacy of patient-related health information through UIUC’s Health Insurance Portability and Accountability Act Privacy and Security Compliance Program; (2) safe handling of Human Cell Lines/Materials in a Research Laboratory for the collection of blood spots, sponsored by the UIUC Institutional Biosafety Committee; (3) technological training, including electronic collection of survey data through REDCap, handling of tablet computers, and tracking of website visits and module completion across enrollees; (4) training in interview techniques, including building of rapport, interacting warmly and respectfully when working with Hispanic/Latino adults, that is, cultural value of *respeto*, consistency in ordering and wording of survey instruments, that is, quantitative methodology, (5) triggering of referrals to attending physician or distribution of resource listings when appropriate (eg, dangerously high levels of BP); and (6) protocol for weekly phone calls and text messages to reinforce web-based curricular content.

Multiple aspects of the intervention are manualized to strengthen the fidelity of the intervention and to ensure that the research staff are conveying identical content, particularly during weekly phone calls and when delivering messages via text. As such, research staff followed predrafted scripts, developed by the principal investigator, all of which followed a standard template as follows: (1) greet participants; (2) provide a brief summary (2-3 sentences) of the curricular content for that week; (3) from the participants’ perspective, inquire of important lessons learned from weekly content; (4) ask of any difficulties in using a tablet computer; and (5) remind participants that the staff are available via phone or email to troubleshoot if any questions or difficulties arise. All weekly text messages were prewritten in Spanish and sent to participants without modification.

Finally, research staff are trained on handling circumstances requiring immediate action and a patient referral to the attending physician. Research staff have detailed instructions, depicted using a graphic decision support tool (ie, decision tree), on the protocol to alert the attending physician if participants displayed elevated symptoms of depression (Center for Epidemiologic Studies Depression Scale ≥16; denoting probable clinical depression) or if they present with exorbitantly high BP levels, that is, ≥180/120 mm Hg. Training of research staff occurs at the outset during study startup, with booster sessions throughout the trial to ensure proficiency, along with immediate guidance when procedural issues are evident.

### Measures

#### Primary Outcome

Measures of sitting and ambulatory BP serve as the primary outcomes for the current *¡Alégrate!* trial. An ambulatory BP monitoring (ABPM) method will be used to capture 24-hour daytime and nighttime BP readings in the natural environment (Ultralite 90217A ABPM from Spacelabs Healthcare); this device has shown adequate reliability and accuracy. We will consider 24-hour mean systolic and diastolic readings. Weighing in at 9 ounces, the ABPM monitors were fitted and preprogramed to automatically inflate over a 24-hour period—specifically, measurements are taken every 30 min during daytime hours (7:00 AM to 11:00 PM) and every 60 min at night (11:00 PM to 6:00 AM). We will additionally use an automatic sphygmomanometer to evaluate sitting BP. This measurement device has been validated across multiple cohort studies, including MESA, NHANES, and HCHS/SOL. Three systolic and diastolic BP readings will be taken with participants in the seated position; mean values will be obtained by averaging the last 2 readings.

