### Planned Analyses

The primary outcome of the *¡Alégrate!* trial focused on prospective changes in B*P* values, that is, both sitting BP and 24-hour ambulatory readings. The first aim was to examine the efficacy of the intervention in reducing B*P* values immediately postintervention (ie, 5 weeks) and at the 12-week follow-up period, that is, Exams 2 and 3. The second aim was to explore whether the intervention leads to significant improvements in psychological well-being and greater adherence to healthy behavioral practices. We will additionally test whether psychological well-being and healthy behaviors serve as mediators when exploring intervention effects on BP control. The third aim is to test intervention effects on circulating markers of inflammation, specifically high-sensitivity C-reactive protein.

Descriptive statistics, at baseline, will summarize participant characteristics for the full sample and stratified by intervention arm. Bivariate tests will be conducted to compare the intervention and control conditions to ensure compatibility across key variables (eg, demographic factors, well-being profiles, etc) and to test the success of the randomization protocol. Discrepancies in baseline values across conditions will inform covariates for inclusion when testing our main hypotheses of interest. In addition, we will document the number of missing observations over time to assess the potential for bias resulting from significant dropout and differential attrition by condition. We will perform independent sample two-tailed *t* tests and/or Fisher exact tests to compare baseline characteristics of enrollees who completed the trial versus those who prematurely dropped out, allowing us to test possible predictors of attrition.

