Given our design and main objective of treatment evaluation, an intent-to-treat analysis will be conducted, where we will consider the data of all participants randomized, with retention of their original intervention assignment. Sensitivity analysis will use multiple imputation procedures across missing values to ensure inclusion of all observations, particularly those resulting from participants who withdraw, are lost to follow-up, or do not complete all assessments. In a supplementary analysis, we will use ordinary or logistic regression (as appropriate, given variable distribution) to implement a dose-response analysis to test whether participation-related factors (eg, number of sessions viewed, rate of homework completion) impact outcomes of interest.

We estimated the sample size requirements of a two-arm randomized trial to evaluate whether our web-based positive psychological intervention resulted in differential and clinically meaningful improvements in systolic BP of 6 mm Hg compared with an attention control condition. A repeated-measures design with systolic BP determination at baseline and 5 and 12 weeks was used. In addition, the following operating characteristics were assumed: (1) a between-subject standard deviation for BP of *σ=12 mm Hg*; (2) a within-subject correlation, *ρ=0.60* (3) a two-sided type I error probability of 0.05; and (4) 80% statistical power. Frison and Pocock [65] argue that adjusting for baseline measures (analysis of covariance) results in a more efficient analysis for a given sample size (larger statistical power). This approach yields an estimate of the required sample size of 28 participants per study arm under equal allocation. Furthermore, assuming a conservative attrition rate of 20%, an updated estimation produces the following sample size of participants per study arm.

[figure not shown]

Stata 15 was used for sample size calculation (*sampsi* command) and all statistical analyses, with effect size estimation derived from published data on the clinical effectiveness of psychotherapeutic interventions to treat hypertension [47,66,67].

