#### Aim 1: Determine the Efficacy of the ¡Alégrate! Web-Based Positive Psychological Intervention in Improving BP Control in Hispanic/Latino People With Hypertension From Baseline, Immediately Postintervention (5 Weeks), and at 12 Weeks After Baseline 

Independent samples *t* tests will be performed using 5-week systolic BP and diastolic BP as the dependent variables, with treatment condition serving as the grouping variable. Other model-based approaches to handle missing data, such as weighted estimating equations, will be implemented. We will also use mixed-effects models to compare changes in BP between the control and intervention arms as measured at baseline, 5 weeks, and 12 weeks. The independent variables include a time variable t (t=0, 5, 12), a dummy variable N (N=1, if PP intervention group; N=0, if attention control), and a cross-product term (t×N). For ambulatory data collected across a 24-hour period, sensitivity analyses will compare mean overall daytime versus nighttime values of BP. All data analyses were conducted using SAS 9.4 software (SAS Institute).

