#### Aim 2: To Test Intervention Effects on Psychological Well-Being and Adherence to Healthy Behaviors and to Subsequently Explore Whether Improvements in Psychological Well-Being and Adherence to Healthy Behaviors Are Responsible for Better BP Control, That Is, Mediation Testing

Similar analytic techniques will be implemented for Aim 2 as used for Aim 1. The interaction of Group×Time will test if greater improvements are evident for psychological well-being and engagement in healthy behaviors (eg, dietary intake and self-reported physical activity) at 5 weeks postbaseline for the treatment arm as compared with the active control group. RM-ANOVA will also be used to examine whether the *¡Alégrate!* intervention is associated with greater improvements in psychological well-being and engagement in healthy behavior. In addition to reporting nominal *P* values, we will document the number of tests conducted and associated Bonferroni correction. Finally, we will conduct mediation analysis to test whether psychological well-being and healthy behaviors serve as intermediates (or mediators) through which *¡Alégrate!* impacts BP control. Tests of mediation will follow the recommendations of Shrout and Bolder to bootstrap product terms using Mplus. Given the dependency of indirect effects on the time interval, for multiwave models, we will compute overall, rather than time-specific, indirect effects.

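### Sitting and 24-hour BP, systolic and diastolic, are all primary at two visits with no decisive test named, while the sample size covers one systolic comparison at 5%

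*Protocol article*

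**What the plan says.** Measures, Primary Outcome, states that "Measures of sitting and ambulatory BP serve as the primary outcomes". For the ambulatory recording, "We will consider 24-hour mean systolic and diastolic readings". For the clinic measurement, "Three systolic and diastolic BP readings will be taken with participants in the seated position". Table 2 has the same two entries under primary outcomes, and the Abstract also names both. Planned Analyses repeats that the primary outcome is "both sitting BP and 24-hour ambulatory readings", and the first aim is judged "immediately postintervention (ie, 5 weeks) and at the 12-week follow-up period, that is, Exams 2 and 3". That makes four measures at two follow-up visits, with no ranking.

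Under Aim 1, independent-samples t tests "will be performed using 5-week systolic BP and diastolic BP as the dependent variables". The same section adds mixed models over weeks 0, 5 and 12 with a time-by-group product term, and weighted estimating equations to deal with missing data. None is called decisive.

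The sample size text in Planned Analyses is built on "differential and clinically meaningful improvements in systolic BP of 6 mm Hg", with SD 12 mm Hg, within-subject correlation 0.60, two-sided error 0.05, 80% power and analysis of covariance. It gives 28 per arm before attrition.

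The only words on multiplicity are under Aim 2 (well-being and healthy behaviors): "we will document the number of tests conducted and associated Bonferroni correction".

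**The concern.** The design and the analysis answer different questions. The sample size presupposes one systolic test with a 5% error rate. The outcome and Aim 1 text offers several BP results that can each be called primary, by more than one method, with no rule for combining them. The document does not say whether success needs all of them, any of them, or a particular one.

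Two things are at stake. If a single significant BP result can be reported as the trial's primary finding, the 5% used for sizing does not apply to that claim. And a mixed pattern, such as sitting systolic BP improved at 5 weeks but 24-hour systolic BP unchanged, has no reading agreed in advance.

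**Working it through.** **Step 1. What single test does the sample size describe?** Inputs from Planned Analyses: difference 6, SD 12, correlation 0.60, two-sided 0.05, power 80%, one baseline and two follow-ups.

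- Variance factor for the mean of two follow-ups adjusted for baseline: (1 + 0.60)/2 − 0.60² = 0.80 − 0.36 = 0.44.
- n per arm = 2 × (1.960 + 0.842)² × 12² × 0.44 / 6² = 27.6, so 28. This matches the stated figure.
- With 20% attrition: 28/0.8 = 35 per arm, 70 in total, as in the Abstract.

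Other forms do not give 28:

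| Analysis | n per arm |
|---|---|
| Baseline-adjusted mean of two follow-ups | 28 |
| Change from baseline, mean of two follow-ups | 38 |
| Baseline-adjusted, one follow-up | 41 |
| Unadjusted mean of two follow-ups | 51 |
| Unadjusted single follow-up value | 63 |

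The design therefore rests on one baseline-adjusted test of the averaged follow-up. Aim 1 lists no such test. Its t test on 5-week values is the last row; at 28 per arm that test has about 46% power.

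**Step 2. Which tests does Aim 1 name?** For each of four measures (sitting systolic, sitting diastolic, 24-hour systolic, 24-hour diastolic): a t test at 5 weeks and a time-by-group term over weeks 0, 5 and 12. Week 12 enters only through the mixed model. This gives four tests on the narrow reading and eight on the full one.

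**Step 3. Chance of at least one p < 0.05 with no effect.** If four tests were independent: 1 − 0.95⁴ = 18.5%. BP measures are correlated, so null test statistics were simulated (400,000 runs per setting) with the document's 0.60 between visits and a common correlation between the four measures. The latter is an assumption, varied from 0.3 to 0.8.

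| Assumed correlation between measures | Four 5-week t tests | 5-week t test plus time-by-group term, four measures |
|---|---|---|
| 0.3 | 17.4% | 31.7% |
| 0.5 | 15.6% | 28.8% |
| 0.7 | 13.1% | 24.4% |
| 0.8 | 11.4% | 21.5% |

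The second column of results is nearly double the first because, with time entered linearly as 0, 5, 12, the slope gives week 5 little weight. The centred times are −5.67, −0.67 and 6.33. The correlation between the 5-week difference and the slope on the same measure is −0.67 × 0.40 / √(72.67 × 0.40) ≈ −0.05. The two tests on one measure are almost independent.

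**Step 4. Cost of splitting the error rate instead.** With the 0.44 factor, a Bonferroni split over two tests (0.025 each) needs 34 per arm (43 with attrition), and over four tests (0.0125 each) 40 (50 with attrition). With 28 evaluable per arm, power for a given measure falls to about 72% and 63%.

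**The case against.** The strongest reply is that the protocol never says one significant result among many would count as success. The 0.05 is a sample-size input, not a stated per-test decision rule, and sizing on systolic BP hints at a lead component. This stands to the extent that the error rates above are conditional on an any-one-counts reading. It does not resolve the matter, because the hint stops short of saying sitting or ambulatory, which visit, or which analysis.

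A second reply is that a testing hierarchy is commonly left to an analysis plan, which is not shown here. That covers missing detail. It does not cover a protocol that fixes several unranked primaries and is sized for a single test outside its own list of Aim 1 analyses. An analysis plan could choose a lead test, but the protocol sections would still have to be reconciled with it.

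A third is that this is a Phase II pilot of initial efficacy. That lowers the cost of a false positive, but the heading of Aim 1 still sets out to determine efficacy.

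Some stronger readings are tempting and not supported:

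- A reader might count t tests at both visits for four measures and quote 22–26% or more as the false positive rate. Aim 1 places t tests at 5 weeks only, and any such figure depends on correlations the document does not give.
- A reader might treat weighted estimating equations as a third competing primary test. The text introduces them as a way of handling missing data.
- A reader might say the primary family alone lacks protection. Aim 3 states no correction either, and Aim 2 promises only to document one alongside nominal P values.

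**Conclusion.** The point holds as an inconsistency within the protocol: four unranked primary BP measures at two visits, no decisive method, and a sample size for one systolic comparison by an analysis that Aim 1 omits. Followed as written, the plan does not secure the 5% error rate used for sizing. If any single result below 0.05 were taken as success, the false positive chance would be about 11–17% on the narrowest reading and about 21–32% for the test set that Aim 1 names. These ranges rest on assumed between-measure correlations of 0.3–0.8, the document's 0.60 between visits, and large-sample null statistics. They are not rates that the protocol states or implies as fixed.

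**What to change.** By dated amendment, before any unblinded look at the data, name one decisive test: one systolic measure, averaged over weeks 5 and 12, adjusted for baseline, at two-sided 0.05. Add that analysis to Aim 1 and say in the sample size text which systolic measure is meant. The stated 28 per arm, 35 with attrition, then needs no change.

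Which systolic measure leads is partly a judgement. 24-hour mean systolic BP is a reasonable choice: it is recorded away from staff, whom Strengths and Limitations describes as aware of assignment, and it is not the entry criterion, which is sitting BP. Automation is not the argument, since sitting BP also uses an automatic device. If it is chosen, first reconcile the monitor descriptions: the Primary Outcome section and Table 2 name different devices with different weights.

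Make the remaining BP measures, visits and methods secondary or sensitivity analyses. If both systolic measures must stay primary, apply Holm across those two.

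Cost: some current primaries become secondary, or, under the two-way split, power for a given measure falls to as low as about 72% with 28 evaluable per arm. The article describes data collection as ongoing and the trial is registered, so the change should be documented as an amendment and not made as a silent edit.
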